## Abstract

The use of physiotherapy (PT) in the hospital emergency department (ED) has shown positive results including improvements in patient waiting time, treatment initiation, discharge type, patient outcomes, safety and acceptability of the intervention by medical staffs. These findings originate from studies that primarily focus on musculoskeletal and orthopaedic conditions. Despite a significant number of people visiting the ED, there is a shortage of literature evaluating PT in the ED for elderly populations. The objective of this study is the evaluate the effect of delivering PT in the ED (versus no delivery) in patients aged 75 and over with ‘falls’ complaints. The main objective is the evaluate the effect on the discharge disposition (discharge home, hospitalization). Secondarily, we will evaluate the effect delivering PT on patient-length of stay, the number of falls at 7 days after admission to the ED, changes between the initial and final medical decision regarding patient orientation, and medical staff satisfaction. This study will follow a prospective longitudinal design involving participants aged 75 years and over. We plan to recruit a total n = 336 patients admitted to the ED with a ‘fall’ chief complaint. After consent, participants will be randomized into either the ‘PT-group’ (receiving a prescription and execution of PT within the ED), or to the ‘no-PT group’ (no delivery of PT within the ED). The PT intervention will involve a standardized assessment of motor capacities using validated clinical examinations, and the delivery of rehabilitative exercises based on individual needs. Outcomes will be recorded from the patient’s medical record, and a phone call at 7 days. A questionnaire will be sent to medical staff. The results of this study will help to determine whether PT might be beneficial for the management of this increasing proportion of individuals who come to the ED.

**Trial registration:** (Trial registration number: ClinicalTrials.gov NCT05753319). https://classic.clinicaltrials.gov/ct2/show/NCT05753319.

## Introduction

Emergency Departments visits have exponentially growth worldwide in the last decades. The annual number of visits to ED in France has doubled between 1996 (10 million visits) and 2022 (20.5 million) [1], overcrowding ED. This increasing demand raises the risk of suboptimal care delivery. Overcrowded ED have been associated with adverse events on i) patients, including delayed assessment and care, increased levels of morbidity and mortality; ii) carers and staff, leading to higher frequencies of medical errors, exhaustion, stress and reports of violence; iii) health systems, resulting in longer inpatient lengths of stay, increased ED readmissions and associated costs (for more comprehensive reviews, see Morley et al. [2] and Rasouli et al. [3]). These findings are even more pronounced when considering older populations. In 2022, 44.8% of the population aged over 75 years were admitted to a French ED for at least one visit, accounting for 17% of all ED admissions in the country, while people >75 years made up only 9% of the total population [1,4,5]. The duration of ED stay is longer for the elderly (34% of admissions treated in less than 4 hours vs 79% for <18 years, 61% for 18–74 years [6]), resulting in higher risks for adverse outcomes [7,8] and poor management [9–11]. Additionally, almost 50% of ED visits by patients aged 75 years and over are followed by a subsequent hospitalization [1,6].

French authorities have announced a series of measures in response to the ED ‘endless’ crisis. These potential solutions incorporate both outpatient and inpatient care, as by utilizing the skills and competencies of paramedical staff in the ED [12]. Emerging evidence indicates that using physiotherapy (PT) in patient care within ED reduces wait/treatment time, improves patient outcomes, and offers possibilities for discharging medical staff to complex situations without increasing the risk of adverse incidents [13–18]. Physiotherapists are also well-received by patients and ED staff, and their actions are seen as an opportunity to enhance the care provided in ED [16,19]. However, these results mainly stem from studies in which physiotherapists primarily managed musculoskeletal and orthopaedic conditions, with a wide variation in practice patterns (e.g. primary/secondary contact health provider) and their responsibilities.

There is a shortage of literature evaluating the effects of PT in ED for non-musculoskeletal chief complaints [20]. Data from our hospital [21] and from Gurley et al. [22] reported that ‘falls’ in older populations might account for up to 40% of PT prescriptions [21] or interventions [22] within the ED. Another retrospective study also emphasized the potential for delivering PT in the ED to ‘fallers’ [23]. However, this study did not allow for an estimation of the specific nature of PT service provided (e.g. assessment and/or therapeutic sessions; location within the ED units) or the effects produced on patient discharge and length of stay.

The number of patients aged 75 years and over presenting to the ED increasing, so as their primary complaint identified as ‘fall’ [6,24–26]. It is also estimated that more than 50% of fall patients presenting at the ED report adverse events: recurrent falls, revisits to the ED with subsequent hospitalisations within 6–12 months [27,28], and up to 15% mortality rate one year later [28]. Given the challenges in caring for the elderly population due to frailty and their higher risk for adverse outcomes after an ED visit, there is a need for special attention on screening/assessment and strategies offered to this population in ED [11,29]. To the best of our knowledge, no study has prospectively estimated the effect of delivering PT to patients aged 75 and over admitted in ED with a chief complaint of ‘fall’.

Therefore, the main objective of this study is the evaluate the effect of delivering PT in the ED (versus no PT) in patients aged 75 years and over for ‘falls’ complaints, on the discharge disposition after their ED visit.

The secondary objectives are to evaluate the effect of the intervention (PT vs no PT) on:

the length of stay (LOS) within the ED and the hospitalthe number of falls recorded within the 7 days after admission in EDthe medical staff satisfaction of PT practice in EDthe changes between initial and final EP decision regarding patient orientation (discharge home, acute care unit, hospitalization)

## Materials and methods

### Study design

This is a prospective open-label, randomized, monocentric, two-arm parallel controlled trial to analyse the effects of the delivery of PT in ED, for patients aged 75 years and over, admitted for ‘fall’ chief complaint. The study is reported according to the Standard Protocol Items: Recommendations for Interventional Trials (SPIRIT) [30]. The SPIRIT diagram and flowchart for participants are provided in Figs 1 and 2, respectively.

**Fig 1 pone.0303362.g001:**
[figure not shown]
SPIRIT Diagram for the study. Abbreviations: ED: Emergency department; PT: Physiotherapy.

**Fig 2 pone.0303362.g002:**
[figure not shown]
Flowchart of the study. Protocol version: v.2, June 2023. Abbreviations: ED: Emergency department; EP: Emergency physician; EU: Emergency Unit; OU: Observation Unit; PT: Physiotherapy.

The accordance with SPIRIT checklist and a trial registration data set are provided in (S1 and S2 Files, respectively). The exact timetable of the different phases of the study is provided in S3 File.

### Study setting

This study will be conducted in the adult ED of University Hospital (CHU) of Nantes between April 6, 2023 and February 29, 2024. This ED is one the largest in France, with an average of 219 daily visits and a total of 78 908 annuals visits reported in 2021 (adult ED). Among these patients, 14.0% are aged over 75 years (national rate: 13.9%) [6,31].

The ED is divided into different sectors (traumatic, non-traumatic, fast-track, resuscitation room). Following an initial triage by a specialized nurse, patients are directed to one of the aforementioned sectors based on their clinical presentations and severity. Then, at the Emergency Unit (EU), the Emergency Physician (EP) conducts an initial clinical exam leading to: i) an initial course of action, including prescription (medical imaging, clinical investigation/assessments, biological analyses), and/or introduction of treatment; ii) and an initial decision for patient orientation depending on the clinical severity, treatment requirement, and the initial evolution of the patient. This may include decisions such as a hospital admission, discharge with follow-up instructions, or referral to outpatient specialist. Another possibility is to admit the patient to an Observation Unit (OU) that is close to the ED. The OU is dedicated for the surveillance after initial clinical examination of patients with unpredictable evolution. For instance, if the evolution indicates a more severe condition than initially thought, the EP can decide to admit the patient to the hospital instead of sending him home (discharge). Similarly, if the condition significantly improves with the introduction of treatment, the initial decision for hospital admission can be re-evaluated [32].

Briefly, patients aged 75 years and over admitted with a chief complaint of a ‘fall’ are first clinically assessed within the EU, to provide a prompt clinical exam, an initial course of action, and an initial decision for orientation. After this first stage, there are three possibilities: (i) the situation is benign and the patient is discharged; (ii) there is a clear indication for hospitalization; or (iii) the clinical situation is unpredictable and the patient can be admitted to the OU for observation/monitoring, treatment, and further assessments. As illustrated in Fig 3, the typical pathway involves patients initially going to the EU where they may be directed to one of the three options: returning home, being hospitalized (in another unit of the hospital), or being transferred to the OU. Once in the OU, these patients may later be directed to either return home or continue hospitalization.

**Fig 3 pone.0303362.g003:**
[figure not shown]
Theoretical mapping of pathway within the ED for a patient ≥75 years presenting for ‘fall’ complaint. Abbreviations: ED: Emergency department; PT: Physiotherapy.

### Recruitment process

The aim is to recruit, as exhaustively as possible, all patients meeting the study’s criteria, over a sufficiently long inclusion period to be representative of the population of elderly patients with falls complaints admitted to the ED of Nantes University Hospital. Preliminary analysis at Nantes University Hospital (in May 2022) suggests that there are around 13 patients/day to be eligible to participate in this study. Based on the daily organization of PT services in the ED and considering approximately that 50% of eligible patient will consent to participate, the aim will be to recruit 4 patients/day. A period of recruitment to last 6 months will be planed for a final recruitment for the trial, that may result for a final recruitment of a total of 336 participants for the trial.

Participants who meet the following criteria will be included:

Age 75 years and over, at the age of admissionAdmission in ED for ‘fall’ chief complaintAble for gait or fall risk assessmentAble to understand the protocol and not verbally object to participation

Participants will not be included in case of being already included into another research protocol, not providing their informed consent or being placed under guardianship/curatorship. They will also be excluded if they present a fall that may require a surgical treatment, or being diagnosed a systematic pathology (e.g. cancer) within the ED.

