### Data analysis and interpretation

An independent statistician will perform will perform the analyses (SAS, 9.4^®^).

A review of data will be conducted at the end of the study, prior to statistical analysis. The aim will be to review the progress of the study, potential problems and classify any minor or major deviations. Analyses will be performed in the *Intention-to-Treat* populations corresponding to all randomized patients. A sensitivity analysis will be conducted on the *Per-Protocol* population. This population will include patients without major deviation.

The variables measured at baseline will be described for all patients in both groups by numbers and percentages for each category for categorical variables and the minimum, maximum, average, standard deviation and quartiles for the quantitative variables. (Table 2).

Primary endpoint: the patient orientation at discharge from the ED will be described and compared between the two groups with Chi-square tests, depending on the ED unit of inclusion (emergency unit: 3 modalities: discharge home, hospitalization, observation unit; observation unit: 2 modalities: discharge home, hospitalization).’

Secondary endpoints: LOS-ED and LOS-hos will be described as mean difference and 95% confidence intervals, and compared between the groups using Student’s t tests. The rate of re-visits to ED for fall complaints (characterized as a new episode of fall whose severity requires a re-hospitalization within 7 days) will be compared between groups using Chi-square test. The changes in the patient’s orientation between initial and final decisions will be compared between the groups using Chi-square test. Satisfaction of ED medical staff will be depicted descriptively.

Due to this ‘pragmatic’ approach, it is not possible to compute a priori statistical calculations. The distribution of patients within both units of the ED (EU or UN), the different modalities of patient discharge (Fig 3), and for each group (PT vs no-PT) make it challenging to determine expected differences between groups for the main outcome. As stated, we aim to recruit, as exhaustively as possible, during the inclusion period.

Any missing data will be described and explained. There will be no imputation done on missing data.

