### Issues related to recruitment

The use of ED is very popular by populations aged 75 years and over for fall complaints. The inclusion criteria aim to facilitate the recruitment within ED, for this study. We anticipate our recruitment flow to be relatively smooth. Any recommendations to the DMC might be made to modify recruitment if judged necessary. The recruitment status will be reviewed every 2 months to determine the likelihood of meeting recruitment timeline. If recruitment is slower than expected, the recruitment period will be extended until recruitment is successfully concluded.

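### Recruitment rate, duration and total disagree: 4 recruited patients per day for 6 months gives about 520 to 728, not 336, and neither the rule for ending recruitment nor the precision at 336 is stated

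*Protocol article*

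**What the plan says.** The Recruitment process section starts from a preliminary count that "suggests that there are around 13 patients/day to be eligible to participate in this study". It takes account of how physiotherapy is organised in the department and of about 50% consent, and concludes that "the aim will be to recruit 4 patients/day. A period of recruitment to last 6 months will be planed for a final recruitment". The total follows in the words "that may result for a final recruitment of a total of 336 participants for the trial". The Abstract presents 336 as the planned total.

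Other sections bear on when recruitment ends:

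- Study setting gives a study window of 6 April 2023 to 29 February 2024.
- Data analysis and interpretation says "we aim to recruit, as exhaustively as possible, during the inclusion period".
- Issues related to recruitment says that, if accrual is slower than expected, "the recruitment period will be extended until recruitment is successfully concluded".

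On statistical planning, Data analysis and interpretation states that "it is not possible to compute a priori statistical calculations". The reason given is that the spread of patients over units, discharge categories and groups makes an expected difference hard to determine. The primary comparison is planned as chi-square tests by unit of inclusion, with three categories in the emergency unit and two in the observation unit.

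**The concern.** The total of 336 is the only planning number for the trial's size, and it is presented as the yield of a daily rate over a stated period. A reader who multiplies the two gets a much larger number, so at least one of the three figures is wrong or a recruiting calendar has been left out.

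This affects the conduct of the trial. If the stated rate is achieved, 336 arrives well before 6 months have passed, and the text does not say whether recruitment then stops or runs to the end of the period. The trial is open-label and recruitment is reviewed every two months, so a single rule fixed in advance is worth having.

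The statement that no prior calculation is possible also leaves the reader without any idea of what 336 patients can show.

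**Working it through.** **Inputs from the protocol article**

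- Rate: 4 recruited per day, with consent already taken into account (Recruitment process). As a check on order, 13 × 0.5 = 6.5 consenting patients per day. The figure of 4 lies below this, in line with physiotherapy organisation limiting it further.
- Duration: 6 months, or 182 days, or 26 weeks with 130 weekdays (Recruitment process).
- Total: 336, or 168 per arm at 1:1 (Abstract, Recruitment process, Allocation).
- Background rate: almost 50% of emergency visits at age 75 and over lead to hospitalization (Introduction).

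**Step 1: try to reproduce 336 as rate × recruiting days**

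| Reading of 6 months | Calculation | Total | Relative to 336 |
|---|---|---|---|
| Calendar days | 4 × 182 | 728 | 2.2 |
| Six 28-day months | 4 × 168 | 672 | 2.0 |
| Weekdays, 26 weeks | 4 × 130 | 520 | 1.5 |
| Weekdays, 24 weeks | 4 × 120 | 480 | 1.4 |

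None gives 336. Working back, 336 / 4 = 84 recruiting days. Over 6 months, 336 corresponds to 336 / 182 = 1.85 per calendar day or 336 / 130 = 2.6 per weekday.

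**Step 2: which inputs would give 336?**

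- 4 per day on 14 days per month for 6 months: 4 × 14 × 6 = 336. No such calendar is stated.
- 4 × 0.5 × 168 days = 336. This applies the 50% consent a second time, after it was used to arrive at 4.

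**Step 3: how much the end rule matters**

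At 4 per day, stopping on the number gives 336, and stopping at 6 months gives about 520 to 728. The window in Study setting is 330 days (about 10.8 months), which may include follow-up and close-out. Over that window, 336 is 336 / 330 = 1.0 per day.

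**Step 4: can precision be computed at a fixed total?**

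This is an illustration for a pooled two-category outcome (hospitalized or not). Assumptions: two-sided 5%, control rate 50%, n = 168 per arm.

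- Half-width of the 95% confidence interval: 1.96 × √(2 × 0.25 / 168) = 0.107, or 10.7 points.
- Power = Φ{[d√n − 1.96√(2p̄(1 − p̄))] / √(p₁(1 − p₁) + p₂(1 − p₂))}, where p̄ is the mean of the two rates and d their difference.
- 50% against 35%: [0.15 × 12.96 − 1.96 × 0.699] / 0.691 = 0.83, so power is 79.7% (340 patients needed for 80%).
- 50% against 40%: [0.10 × 12.96 − 1.96 × 0.704] / 0.700 = −0.12, so power is 45% (776 patients needed for 80%).
- Smallest drop with 80% power: 15.1 points at a control rate of 50%, and about 14 to 15 points over control rates of 40% to 60%.

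Within one unit, again for two categories and with assumed shares of the patients:

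| Share of patients in the unit | n per arm | Difference with 80% power | Half-width |
|---|---|---|---|
| 50% | 84 | about 21 points | 15.1 points |
| 25% | 42 | about 29 points | 21.4 points |

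**The case against.** **The total is worded as a forecast, and the slip may be one of wording.** The text says 336 may result, and the exact match with a second use of the consent rate suggests that 4 per day could have meant patients approached. That is plausible, but the sentence as printed uses consent first and speaks of patients recruited. A forecast must still follow from its inputs, and the Abstract adopts 336 as the plan. What stands of this objection is that nobody outside the team can say which figure is wrong. A reader might infer that 14 recruiting days per month was intended, but nothing in the article supports that calendar.

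**The passages on ending recruitment can be read together.** A reader might count three competing stopping rules. That goes too far. Recruiting exhaustively mainly describes sampling for representativeness, and the extension applies only if accrual is slow. A fair combined reading is a target of 336, planned over 6 months and extended if needed. What remains open is what happens when accrual is at or above the stated rate.

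**A conventional sample-size calculation does need an expected difference.** The authors give a specific reason for not having one, and that reason stands. It does not rule out a statement of precision or of detectable difference at a fixed total.

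**The illustrative figures are not the planned analysis.** This also stands. The 50% rate covers all emergency visits at age 75 and over. The trial takes falls only, requires ability for gait or fall-risk assessment, and excludes falls that may need surgery. The planned tests are by unit, the emergency-unit outcome has three categories, and the article gives no split between units.

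**Conclusion.** The point holds. Rate, duration and total are inconsistent by a factor of about 1.5 (weekdays) to 2.2 (calendar days), and 336 is matched only by inputs that the article does not state. That result is plain arithmetic on the article's own figures. Whether the number or the calendar governs is unsettled, and at the stated rate this changes the trial's size by the same factor.

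The claim that no prior calculation is possible is too strong, but only in the sense that precision can be given under assumptions. The figures of about 10.7 points (half-width), 15 points (80% power) and 45% power for 10 points rest on a pooled two-category outcome, a two-sided 5% level and a control rate borrowed from a wider population. Precision within a unit will be worse by an amount that depends on the unknown split.

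A reader might also infer that recruitment would be stopped or extended on an impression of the results, or that a non-significant result would be reported as no effect. The article supports neither. It describes no interim comparison of outcomes, and the two-monthly review is described as covering recruitment flow and adverse events, with recommendations on safety and protocol modifications. It does not say how a null result would be interpreted.

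**What to change.** 1. Correct whichever of the daily rate, the recruiting days or the total is wrong, and state the recruiting calendar, so that the product gives the planned total.
2. State one rule for ending recruitment that does not depend on outcome data: whether reaching 336 or the calendar governs, with extension only if accrual is slow. Bring the Abstract, Study setting, Recruitment process, Data analysis and interpretation, and Issues related to recruitment into line with it.
3. Replace the statement that prior calculation is not possible with the precision or detectable difference at the planned total. Give it for the comparison actually planned, by unit of inclusion and with the emergency unit's three categories, over a range of assumed base rates and unit splits. The figures above illustrate the method and should not be inserted as they stand.

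The cost is text and a short calculation, with no extra patients. The drawback is that the trial's stated capability will look less favourable than silence on the matter suggests.
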